## Abstract

**Clinical trial registration:**

ClinicalTrials.gov, identifier NCT 05909202.

## Introduction

1

Hematopoietic stem cell transplant (HSCT), also called bone marrow transplant, is a procedure to treat malignancies and non-malignant conditions by replacing dysfunctional bone marrow with healthy stem cells from the patient’s own body (autologous) or a donor (allogeneic) (1). Since 2016, an average of more than 22,000 HSCTs have been performed in the United States each year (2). Caring for a HSCT recipient is burdensome as the recipient is at risk for complications (e.g., graft versus host disease and cytopenia) and requires extensive support during and after treatment (3). Family caregivers of HSCT recipients may feel rewarded while taking on caregiving tasks, but they may also experience stress and stress-related symptoms (4, 5). Frequently reported symptoms include fatigue, sleep disturbance, depression, anxiety, and impaired cognition, which tend to occur concurrently (4–7). Stress and symptoms experienced by HSCT caregivers can negatively impact health outcomes for both caregivers and the recipient. However, there are limited resources available to address stress and symptoms in HSCT caregivers.

Virtual reality (VR) is a promising technology that can be used to develop interventions to manage stress and symptoms in HSCT caregivers. VR is a type of extended technology, defined as “a simulated three-dimensional environment that enables users to explore and interact with a virtual surrounding perceived through the user’s senses (8).” People mainly interact with virtual environments using special equipment such as a headset with a screen inside and a controller with sensors fitted (9). As VR has become more immersive, affordable and portable, various areas, including education, entertainment, and healthcare, are using this technology (10, 11). The application of VR in healthcare includes training for students and medical professionals and treatment and wellness uses such as stress and symptom improvement (e.g., pain management) (12). Many studies that developed VR-based interventions simulated nature environments (e.g., forest, beach, lake) on a virtual platform and tested the effects of experiencing this nature on health-related outcomes (10, 13, 14). These studies have shown positive effects in reducing pain, stress, and unpleasant psychological symptoms (10, 13, 14).

Nature experience in VR might also help relieve stress and symptoms in HSCT caregivers. However, there are limited studies examining the effectiveness of VR-based interventions in family caregiver populations. Existing intervention studies to address stress and symptoms in family caregivers often took a mindfulness approach and included yoga, breathing exercise, and meditation as components of the program (15–17). These intervention programs necessitated a lot of time and effort from caregivers who may find it difficult to be away from their care recipients. Stress reduction interventions using VR technology may allow family caregivers to use the intervention at their desired location and time. In addition, integrating biomarkers into VR intervention studies for family caregivers would allow for a more comprehensive assessment of caregivers’ response to VR interventions than relying solely on self-report measures (18, 19). As caregiving is a potential stressor that may contribute the development of cardiometabolic and inflammatory disease (20, 21), it is important to include biomarkers that can objectively measure stress responses (e.g., cortisol, α-amylase, osteocalcin, Oxytocin), and cardiometabolic (e.g., lipoprotein particle profile) and immune function (e.g., cytokine) in cancer caregiving research.

This research is guided by a conceptual model based on the Attention Restoration Theory (ART; 22, 23) and the Theory of Unpleasant Symptoms (TOUS; 24). According to the ART, experiencing restorative environments induces involuntary attention engagement, leading to the restoration of directed attention and the relief from directed attentional fatigue (22, 23). The ART explains that interaction with nature environments allows directed attention to get rest and recover while using involuntary attention, which can be beneficial for performing tasks and reducing stress and negative moods. Restoration of directed attention primarily occurs in nature environments but may also occur in some urban settings with sufficient restorative qualities, such as historical sites or museums (22, 23, 25). The TOUS assumes that symptoms can occur individually or concurrently, and these symptoms form a feedback loop that also affects individual factors that contribute to the symptom experience (24, 26). In our conceptual model (see **Figure 1**), caregiving stress leads to caregivers’ multiple symptoms, including fatigue, sleep disturbance, depression, anxiety, and impaired cognition. Caregiving stress is closely related to caregiver characteristics and care recipient characteristics. Each symptom experienced by caregivers likely interacts with each other.

**Figure 1 f1:**
[figure not shown]
Conceptual model of factors influencing caregiving stress and symptoms. VR, virtual reality.

A growing body of literature reveals that a pleasant and immersive nature virtual environment may contribute to facilitating relaxation and stress management compared to urban scenes (27–29). These benefits from being exposed to virtual nature are generally consistent with those from actual nature (27). However, controversy still exists on the advantage of virtual immersion in nature versus traditional 2D mediums (non-immersive) (27). Furthermore, no published studies have examined the effectiveness of nature experience in VR, focusing on family caregivers of cancer patients. Building upon the feasibility study with the nature-based immersive VR intervention and the comparison condition (non-immersive VR program) have been developed in HSCT caregivers. We aim (1) to evaluate the feasibility and acceptability of the nature-based immersive VR program; (2) to examine the effectiveness of a nature-based immersive VR program on stress compared to a non-immersive nature-based VR in HSCT caregivers; and (3) to explore relationships among variables, including but not limited to symptoms, HSCT caregiver characteristics, HSCT recipient characteristics, and biomarkers. We propose that the nature-based VR intervention will effectively relieve caregiving stress in HSCT caregivers.

## Methods and analysis

2

### Design

2.1

The proposed study is a single site, two-phase study targeting allogeneic HSCT caregivers. The Phase I of the study is a single-arm pre-post design to assess the feasibility and acceptability of the nature-based immersive VR program in HSCT caregivers. The Phase II of the study is a prospective randomized controlled trial (RCT) design to examine the effectiveness of the nature-based immersive VR program on stress and symptoms compared to a nature-based non-immersive VR program in the target population. This study followed the Consolidated Standards of Reporting Trials (CONSORT) reporting guidelines for RCTs (**Supplementary Table S1**). In Phase I, all caregiver participants will be given the nature-based immersive VR program. We hypothesize that the majority of caregiver participants will perceive the nature-based immersive VR program as usable, safe, and restorative and show improved levels of stress and symptoms at Time 4 (Day 28) compared to Time 0 (Day 0). In Phase II, caregiver participants will be randomly assigned to one of two groups: nature-based immersive VR program (Active VR) and nature-based non-immersive VR program (Sham VR). We hypothesize that caregiver participants assigned to Active VR will show improved levels of stress and symptoms at Time 4 compared to those assigned to Sham VR. If we identify any weaknesses or gaps in the results of Phase I, such as dissatisfaction with the program (e.g., content, length of the video, difficulty in use) and discomfort with the headset, we plan to make appropriate adjustments prior to initiating Phase II.

### Participants

2.2

The research protocol will include adults (18 years and older) who serve as a primary caregiver for an adult (18 years and older) planning to undergo an allogeneic HSCT at the NIH Clinical Center. If more than one caregiver is planned for the transplant recipient during the transplant phase, only one primary caregiver will be eligible to participate in this study. Phase I will enroll up to 15 caregiver participants, and Phase II will enroll up to 94 caregiver participants (please see “2.6 Data analysis and sample size estimation” section). Inclusion/exclusion criteria are as follows:

#### Inclusion criteria

2.2.1

Ability to understand and the willingness to sign a written informed consent document.Age 18 years and older.Serving as a primary caregiver for an adult patient (18 years and older) undergoing their 1^st^ allogeneic HSCT at the National Institutes of Health (NIH) Clinical Center during the four-week study period.Ability to read, speak, and understand English.Access to necessary resources for participating in online survey (i.e., computer, laptop, tablet, smartphone, internet access).

#### Exclusion criteria

2.2.2

Serving as a paid caregiver for the patient.Not agreeing to follow the study procedures.Recent use of immersive VR programs for stress relief and/or entertainment (more than 2 days/week within the past 3 months).Participation in another stress-reduction type interventional study within the past 3 months.Having a medical condition that is prone to frequent nausea or dizziness.Current or past history of seizure, chronic migraines, epilepsy, claustrophobia, panic disorder, post-traumatic stress disorder, generalized anxiety disorder, major depressive disorder or other known severe neurological or mental health disorders.Being sensitive to flashing light or motion.Having a balance disorder such as vertigo or cybersickness.Having another medical condition or injury that may prevent use of VR headset and/or VR software (e.g., visual or hearing problems, open sores, wounds, skin rash on face, or active infection).Self-reported diagnosis of Opioid, Cocaine, and/or Cannabis use disorder in the past year.

### Interventional methods

2.3

#### Nature-based immersive VR program (active VR; phase I/II)

2.3.1

Participants will receive a VR headset and be asked to perform the intervention for 20 minutes per days for four weeks. The intervention dose (20 minutes) was selected to decrease the risk of developing cybersickness. More prolonged exposure to VR is associated with a higher risk of cybersickness (30). In a systematic review of VR relaxation studies for the general population (28), 14 out of 19 studies administered a single-session format intervention for 20 minutes or less. There could be a novelty bias in VR research as it is an emerging technology in the health care field. Therefore, considering that caregiving stress is a type of chronic stress, we intend to set the intervention duration longer. The 4-week intervention duration was chosen based on two recent ongoing trials testing the effects of VR nature or relaxation for four weeks (31, 32).

For use in this study, we developed the nature-based immersive VR program software called “Nature VRelax.” All caregiver participants in Phase I and participants assigned to Active VR in Phase II will receive the Nature VRelax. The Nature VRelax contains 13 videos consisting of 360° high-definition video clips with nature sounds produced by Atmosphaeres ^1^. The video clips produced by Atmosphaeres have been tested in previous studies with different groups of patients and healthy adults; cybersickness, nausea, and dizziness were reported in several participants, but no serious adverse events occurred (33–36). Participants will select VR content from the pre-loaded 13 options on the VR headset, which fall into one of the following categories:

Nature (11 videos): Nature scenes with pure nature sounds filmed in various locations (e.g., beach, river, meadow)Travel (2 videos): Scenes filmed in various historical sites and city attractions (e.g., London, Paris)

A complete list of VR experiences will be offered to study participants is listed in **Figure 2**.

**Figure 2 f2:**
[figure not shown]
Themes and screenshots of virtual reality (VR) experiences available to study participants.

#### Nature-based non-immersive VR program (Sham VR; phase II only)

2.3.2

Participants assigned to Sham VR in Phase II will receive a nature-based non-immersive VR program. The Sham VR program contains 3D nature pictures with nature sounds pre-loaded on the VR headset. When the device is turned on, the nature photographs will be played automatically (one minute per photograph).

#### VR headset

2.3.3

This study will use the Pico G3^2^ that delivers videos or computer-generated images and sounds to create an immersive environment. Pico G3 is a stand-alone head-mounted display that does not require a smartphone or a computer to run and is easy to use with an orientation-tracked controller or a handsfree control option. We will only provide the Nature VRelax pre-loaded videos on the VR headset and lock other external contents.

### Procedures

2.4

A screening visit will be conducted for eligible caregivers who agree to participate. During the screening visit, eligibility will be assessed, and informed consent will be obtained if a caregiver meets all eligibility criteria. Time 0 baseline visit for all participants will occur within seven days of the HSCT infusion in a quiet room on the oncology/transplant unit at the NIH Clinical Center. During the Time 0 baseline visit, all participants will be trained on how to use the assigned VR program, including wearing the VR headset and navigating the VR videos. The research staff will guide the participants on the VR headset use to familiarize themselves with the device and allow them to test it on their own. Once the participants feel comfortable with the VR headset, they will experience the 15-minute video, which we developed for the initial testing purpose, under the supervision of the research staff. The research staff will monitor any issues or adverse events (AEs) associated with the VR program and will address any questions that the participants may have.

Following Time 0 baseline visit, participants will be instructed to use the Nature VRelax program for a maximum of 20 minutes, daily for four weeks. Once they complete practicing a 20-minute video, the VR program will be locked for the day and automatically reset at midnight. If they are interrupted during the session, they can resume or stop. Participants will be instructed to use the VR program in a static sitting position in a quiet place. Participants can connect a listening device (e.g., earphones, headphones, earbuds) to the VR headset as needed. The program can be used with or without a Wi-Fi connection. Participants will be informed that use usage of the program will be tracked on the VR headset. Participants will complete a daily use log. They will be instructed to discontinue use and notify the research staff immediately if they experience any unpleasant side effects, such as dizziness or nausea.

At each time point, all participants will be asked to complete a survey that will be delivered via the Research Electronic Data Capture (REDCap) system.^3^ The surveys at Time 0 (Day 0) and Time 4 (Day 28) will take about 20 to 30 minutes, and the surveys at Time 1 (Day 7), Time 2 (Day 14), and Time 3 (Day 21) will take about 3 to 5 minutes. The participants will be invited to a phone call follow-up at Time 1 and an exit interview at Time 4. Clinical assessments will be performed at Time 0 baseline visit and at Time 4 visit. Saliva samples will be collected three times at Time 0 baseline visit (pre-initial VR program, immediately post-initial VR program, 20 minutes post-initial VR program) and at Time 4 visit (pre-VR program, immediately post-VR program, 20 minutes post-VR program). To index cortisol awakening response, the participants will be instructed to collect three saliva samples (immediately post-awakening, 30 minutes post-awakening, nighttime) within three days of Time 0 and Time 4. In Phase II, blood samples will be collected at Time 0 baseline visit and at Time 4 visit. The schedule of activities or schema of Phase I and II are presented in **Figures 3**, **4**.

**Figure 3 f3:**
[figure not shown]
Research design and procedure (Phase I).

**Figure 4 f4:**
[figure not shown]
Research design and procedure (Phase II).

#### Randomization

2.4.1

In Phase II, all caregiver participants will be randomized into either Active VR group or Sham VR group using permuted block randomization with an allocation ratio of 1:1. All investigators will remain blind to the randomization scheme until each study participant is deemed eligible and signs the consent form. Once each participant is randomly assigned, the participant and the research team members will be aware of the group assignment status.

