### Data analysis and sample size estimation

2.6

For Phase I, a sample size of 12 is considered since this number is recommended to justify the study feasibility and precision of the mean and variance (53). To account for a 20% attrition rate, Phase I study will enroll up to 15 caregivers. To estimate a sample size for Phase II study, power analysis was performed based on the primary outcome. We used a two-sided hypothesis that the stress level will differ between Active VR group and Sham VR group. In order to detect a difference between Active VR group and Sham VR group, we will need 39 caregiver participants in each group and a total sample size of 78 based on an effect size of 0.6 and correlation of 0.80 between two time points from our previous stress reduction study (54), with 80% power and type 1 error of 0.05. To account for a 20% attrition rate, this study will enroll up to 94 caregivers.

In Phase I, feasibility, acceptability, and perceived restorativeness will be evaluated using descriptive statistics appropriate to the levels of measurement. Friedman test or linear mixed models will be used to test changes in stress measured weekly from Time 0 to Time 4. In Phase II, linear mixed repeated measures analysis will be used to analyze the effects of Active VR on stress compared to Sham VR. Any demographic covariates will be included in the model if significantly associated with the outcomes and significantly different between the two groups. All qualitative data, including written comments on open-ended questions and transcriptions of audio from the phone call follow-up and exit-interview, will be subjected to coding and qualitative data analysis.

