Despite the innovativeness and strengths of this study, a few limitations should be noted. First, only family caregivers of people receiving allogeneic HSCT at the NIH Clinical Center, a unique clinical research hospital setting providing care to those enrolled in research protocols with no charge to the research participants, are recruited to the study; thus, generalizability may be limited with respect to caregivers of other disease groups or patients receiving traditional care in general hospitals or clinics. Furthermore, this study recruits only English-speaking caregivers, which ultimately may limit generalizability to caregivers of other racial or ethnic backgrounds. In addition, in this study, once each participant is randomly assigned, the participant will be aware of the group assignment status. Therefore, the expectancy effect is not avoidable, which might influence participant behavior and the outcomes. A double-blind RCT design should be considered to get a more concise estimate of the specific effects of the intervention in the future. Lastly, this study will only examine the short-term effects (four weeks) of the intervention on stress and symptoms. Therefore, any longer-term effects of the nature-based VR intervention could not be captured in the present study. A more prolonged follow-up could further inform the long-term intervention effects in future trials and large-scale efficacy testing.

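### Section 2.4.1 makes every Phase II assignment known to the research team and reserves no masked role, although only the staff who deliver the program need to know the arm

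*Protocol article*

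**What the plan says.** Section 2.4.1 (Randomization) has two parts. Before assignment there is concealment: "All investigators will remain blind to the randomization scheme until each study participant is deemed eligible and signs the consent form". After assignment there is disclosure: "the participant and the research team members will be aware of the group assignment status". No role is excepted.

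Section 2.6 (Data analysis and sample size estimation) describes the later work. For the Phase II comparison, "linear mixed repeated measures analysis will be used to analyze the effects of Active VR on stress compared to Sham VR". Demographic covariates enter that model if they are significantly related to the outcomes and differ significantly between the groups. Open-ended comments and "transcriptions of audio from the phone call follow-up and exit-interview, will be subjected to coding and qualitative data analysis". The section does not say who does either task.

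Sections 2.5.9 and 2.5.10 list the saliva and blood assays without naming the laboratory or describing its masking.

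The Discussion (section 3) gives as a limitation that "once each participant is randomly assigned, the participant will be aware of the group assignment status" and links this to an expectancy effect. It then says: "A double-blind RCT design should be considered to get a more concise estimate of the specific effects of the intervention in the future". It does not mention the team's awareness.

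**The concern.** The participant's knowledge of the arm and the team's knowledge of the arm are different sources of bias. The first acts through the participant's own behaviour and answers, and the article concedes it. The second can act after the data are collected, when someone decides which covariates to screen, which observations to exclude, how to specify the model, how to handle a sample or how to code a remark. Masking can limit the second source even in a trial where participants cannot be masked.

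The disclosure is a stated rule, so it is more than a detail that a condensed article has left to another document. As worded, it gives no basis for keeping anyone on the team masked, including people who may never meet a participant. What is at stake is the credibility of the analysis decisions and of the biomarker results, which the Discussion presents as the objective complement to self-report.

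**Working it through.** No figure in the article depends on this rule. The Phase II sample size (39 per group, 78 in total, up to 94 enrolled) would be the same with or without masked staff, as would alpha and power. The check is therefore a comparison of each task with what it requires.

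1. **Training and the first session.** Section 2.4 has research staff train participants on the assigned program and supervise an initial video. These staff must know the arm.

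2. **Saliva collection at the visits.** Section 2.4 times the visit samples before, immediately after and 20 minutes after a VR session at Time 0 and Time 4. Staff who collect them are likely to see which program is running, so masking at collection is not realistic.

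3. **Assays.** Cortisol, α-amylase, osteocalcin and oxytocin in saliva, and lipids and cytokines in blood, are measured from tubes. Nothing in sections 2.5.9 or 2.5.10 requires the assayer to know the arm. A study ID is enough.

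4. **The mixed model.** Fitting it requires the two groups to be distinguished, not named. The same holds for the covariate rule in section 2.6: whether a covariate differs between groups can be tested with arms labelled A and B. Coded arms are therefore compatible with the analysis as planned.

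5. **Transcripts.** Coding does not require an arm label, but the content will often give the arm away. Active VR participants choose among 13 videos (section 2.3.1), while Sham VR plays photographs automatically at one minute each (section 2.3.2). Masking of coders can only be partial.

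6. **The stated limitation.** Section 2.4.1 names two parties who will know the arm, the participant and the research team. The Discussion carries over only the first.

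Of these tasks, only delivery of the program requires the arm. Analysis and assay can be masked, and coding can be masked in part. The rule in section 2.4.1 draws none of these distinctions.

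**The case against.** The strongest reply is that the phrase in section 2.4.1 is an ordinary description of an open-label trial, and that tube labels, batch order and arm-coded datasets belong in a laboratory manual or SAP that is not shown. Part of this stands. A reader might infer that the people who assay samples, fit the model and code interviews are in fact unmasked. The article does not say so: it does not identify them, and an outside laboratory may not count as part of the research team. What remains is that the article states a disclosure rule without exception, and a later document that masked an analyst on the team would contradict it as worded.

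A second reply is that the consequence is small. This also stands in large part. Stress is self-reported through REDCap by participants who know their arm, no observer-rated outcome is described, the biomarkers are laboratory assays, and the qualitative coding does not feed the stress comparison.

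A reader might also infer that an unmasked analyst inflates the type I error of the primary comparison by a calculable amount. The documents do not support a figure. Section 2.6 sets an entry rule for covariates and does not allow a free search. A search for the smallest two-sided p-value would give the same answer with arms coded A/B, because swapping labels leaves that p-value unchanged. Coding the arms prevents choices guided by the direction of benefit. Protection against undirected searching comes from finalising the model before the codes are broken.

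Finally, a reader might suppose that section 2.6 leaves biomarker cleaning to unmasked staff. It says nothing about biomarker cleaning or outliers.

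**Conclusion.** The point holds in a limited form. Section 2.4.1 makes each Phase II assignment known to the research team without exception and reserves no masked role, although only the staff who deliver the program need the arm. The Discussion acknowledges participant awareness alone.

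Its size cannot be expressed as a number from the document. The likely benefit of a change is modest, because masking staff leaves self-report bias in the primary outcome untouched. The conclusion rests on reading the phrase about research team members as covering at least the trial's own analysis staff. If analysis and assays are already done on coded data, the remaining defect is wording that says otherwise. In either case this is a cheap improvement and does not invalidate the trial.

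**What to change.** - **Section 2.4.1:** state that, after randomisation, the arm is disclosed only to the participant and to the staff who train and support participants on the program.
- **Analyst:** supply a dataset with arms coded A/B until covariates, exclusions and model are final, and only then release the code. Hold back any usage record that would reveal the program.
- **Assays:** label saliva and blood tubes with study ID only, and include both arms in each batch.
- **Transcripts:** where practical, send them to coders without arm labels, accepting that content will often reveal the arm.
- **Discussion:** add the remaining staff awareness to the limitations, beside the participants' awareness.

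The cost is small but not nil: revised wording, an arm-code file kept apart from the analyst, and some care in labelling and batching. It needs no extra participants or visits.
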